## Abstract

**Background:**

The nonlinear nature of contagious diseases and the potential for exponential growth can be difficult to grasp for the general public. This has strong implications for public health communication, which needs to be both easily accessible and efficient. A pandemic is an extreme situation, and the accompanying strict societal measures are generally easier to accept if one understands the underlying reasoning behind them. Bringing about informed attitude change and achieving compliance to strict restrictions requires explanations of scientific concepts and terminologies that laypersons can understand.

**Objective:**

The aim of the project is to develop effective, evidence-based modes of video communication for translating complex, but important, health messages about pandemics to both the general population and decision makers. The study uses COVID-19 as a case to learn and prepare society for handling the ongoing and future pandemics, as well as to provide evidence-based tools for the science communication toolbox.

**Methods:**

The project applies a mixed methods design, combining qualitative methods (eg, interviews, observational studies, literature reviews) and quantitative methods (eg, randomized controlled trials [RCTs]). The project brings together researchers from a wide range of academic fields, as well as communication industry professionals.

**Results:**

This study has received funding from the Trond Mohn Foundation through the Research Council of Norway’s “COVID-19 Emergency Call for Proposals” March 2020. Recruitment and data collection for the exploratory first phase of the project ran from February 2021 to March 2021. Creative communication work started in May 2021, and the production of videos for use in the RCTs in the final phase of the project started in September 2021.

**Conclusions:**

The COVCOM project will take on several grand challenges within the field of communicating science and provide evidence-based tools to the science communication toolbox. A long-term goal of the project is to contribute to the creation of a more resilient health care system by developing communication responses tailormade for different audiences, preparing society for any future pandemic.

**International Registered Report Identifier (IRRID):**

DERR1-10.2196/34275

## Introduction

A pandemic is an extreme situation, and extreme measures are needed to combat it. Although similar numbers of people die annually in traffic or from cancer, the number of people who catch a contagious disease can grow at a rapidly increasing rate. This nonlinear nature of contagious diseases and the potential for exponential growth can be difficult to grasp for the general public. At the same time, this feature of contagious diseases brings about a need for measures that are not only rapid but also often radical. This has strong implications for public health communication, which needs to be both easily accessible and efficient. 

During the COVID-19 pandemic, scientific knowledge from various fields of health research has been at the heart of decision-making. Strong preventive and societal measures—with substantial implications on peoples’ lives—have been central to combating the pandemic. Such measures are generally easier to accept if one understands the underlying reasoning behind them [1-3], and bringing about informed attitude change and achieving compliance to strict restrictions thus require explanations of scientific concepts and terminologies that laypersons can understand. Therefore, in order to effectively tackle pandemics, the provision of large-scale information outreach is imperative.

However, how to do this—or how *not* to do it—is poorly understood, with several grand challenges, sparse research within the field, and limited available empirical evidence for making generalizations [4,5]. Systematic reviews [6-9] have found multiple knowledge gaps in pandemic risk communication, for example how risk perception is framed by competing narratives, the lack of in-depth learning from past experiences [8], and slim evidence of the effectiveness of pandemic risk communication [6].

Guaranteeing the flow of information to engage stakeholders is important [9]. Different stakeholders (eg, policy makers, infection control bodies, primary and specialized health care providers) need a common understanding of risk, risk implications, and consequences. This implies that the understanding of key scientific information, and the lack thereof, might facilitate understanding of why national and international societies have not been able to learn from the past and prepare for predicted catastrophic pandemics like COVID-19 [10].

Although crisis communication is an established research field within leadership [11], little is known about the communication of the science upon which leadership and decision-making are based. In the COVID-19 pandemic, this typically entails health science topics related to contagious diseases, including mathematics, epidemiology, risk, medicine, and health. Establishing evidence-based communication that helps facilitate understanding, attitudes, and risk behaviors, and what works for whom, is essential.

The first empirical gap analysis in the field of science communication—including ~3000 papers—identified several grand challenges [4]. First, the field is mostly limited to one-off studies, and there is a need for longitudinal, experimental, comparative, and wider systemic research to understand how contents and channels, actors, and audiences interrelate. Second, the field is caught in disciplinary structures, and the opportunity for interdisciplinary integration has not been seized. Third, there is a lack of transfer and collaboration between researchers and practitioners, and getting practitioners involved in the research has been suggested to bridge the divide. Randomized controlled trials (RCTs) in science communication are few, with retrospective analyses being the norm. The move toward evidence-based science communication, inspired by the impact of evidence-based medicine over the past decades, has been called for [5]. Experimental studies, capable of invalidating previously accepted practices and replacing them with new ones that are more accurate and effective [12], is an integral part of achieving this.

All communication takes place within a continuously changing culture, and narratives, images, and metaphors that worked yesterday might not work today. This must be taken into account when creating health science communication. *How* you say something is as important as *what* you say. Arts is central for outreach [13], and in March 2020, the World Health Organization (WHO) sent out an open global call to creatives to help with communication in the COVID-19 pandemic [14,15]: Creativity in health science communication is a necessity. It is however poorly understood and underused.

The population’s media habits have changed rapidly in recent years. Driven by social media and smartphones, each citizen can now choose on what to spend their time. Video consumption is increasing, and video makes up an estimated 80% of all internet traffic [16]. YouTube, the world’s largest video site, has 2 billion monthly users, with >500 hours of content uploaded every minute [17]. In the United States, YouTube on mobile alone reaches more 18- to 49-year-olds than any cable TV network [18]. However, despite the scale of video consumption, there is little extant evidence to guide the effective use of video for relaying complex health messages. It is well-known in risk and public health communication that trust is key [19,20], and there is a growing body of research on narrative-based methods and digital storytelling within medicine and health [21,22]. However, much research remains before we fully understand how to best utilize the video format for effective public health communication.

Film is a powerful communication format, frequently used in advertising and popular culture. It is a collective process in which screenwriters, directors, cinematographers, set designers, and professional performers come together to tell a story using moving pictures. Artistic choices are central to filmmaking but are rarely considered when communicating science through film. In an analysis of 400 science videos on YouTube, videos generally fell into 1 of 4 categories: video-blog, voice-over animation, recorded presentation, or interview [23]. Notably, none of the most viewed videos on YouTube in 2019 fell into any of these 4 categories. That is, the video styles most often used by science communicators are not the video styles that tend to attract large audiences, indicating that there is something to be gained by exploring other creative means when producing videos in order to attract larger—and other—audiences when communicating scientific knowledge. In order to create effective science communication, interdisciplinary collaboration of experts from disciplines with different norms and practices is needed [24]. Achieving this is challenging, and the field remains immature.

To tackle the grand challenges within the field of science communication [5], the current project takes an interdisciplinary approach to developing effective communication for pandemics. Creating effective science communication requires collaboration between not only scientists with expert knowledge in the subject matter and in communication [25] but also actual communicators. This study brings together experts from a wide range of fields, including researchers from health studies, humanities, risk, societal safety, medicine, nursing, public health studies, psychology, visual communication, epidemiology and statistics, as well as mass media professionals, communicators, and filmmakers, in order to ensure first-hand cultural know-how for contemporary communication. This is done order to move from experience to evidence-based communication.

The primary objective of the study is to use video to develop effective, evidence-based modes of communication for translating complex, but important, health messages about pandemics. The study uses COVID-19 as a case to learn and prepare society for handling the ongoing and future pandemics, as well as to provide evidence-based tools for the science communication toolbox. This will be achieved through the following secondary objectives:

Identify communication strategies and key topics about pandemics that public health scientists and officials need to communicateExplore communication strategies and artistic dimensions in filmmaking for the creation of effective science communication videos aimed at lay viewers, focusing primarily on the adult part of the Norwegian speaking population with a general primary school level understanding of scienceTest the effect of these videos through controlled experiments, coupling communication to learning outcome and individual differences such as attitude(s) and compliance towards the topic(s), exploring also sociodemographic variablesIdentify the features of the most effective videos on a mass communication scale in collaboration with national mass media broadcasters

We hypothesize that shorter, props-driven videos will outperform longer, more static and scientifically focused videos in terms of comprehension of the topics communicated, while trust will be higher in the latter. For intensions, behavior, and behavior change, we hypothesize that narratives and metaphors will be more effective than the factual scientific information itself. Further, optimizing communication for accessibility by reducing scientific precision will not significantly reduce comprehension, intensions, or active behavior. Finally, observed effects will vary according to the demographic characteristics of the receiver.

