#### Randomized Controlled Trials

In WP3, we will perform 2 RCTs with a factorial between-subjects experimental design including various factors related to the video communication. The first RCT will assess nonvisual factors in health communication videos such as the effect of the video super of the presenter (ie, whether the person on screen is labeled as “Professor” or “Citizen” in the text at the bottom of the screen) or whether the message presented is neutral or includes a “call to action” (ie, whether the presenter merely delivers factual information or also encourages the viewer to act). The final choice of nonvisual factors will be informed by work in the preliminary phases of the project. Assessing the effect of such nonvisual factors will be done by having an actor recite different scripts to the camera. The second RCT will use the videos developed by professional video creators in WP2.

The videos will be screened for representativeness of the population. After consent, participants will be randomized to different videos and between-factors conditions. A link will lead them to a web page where the procedure is explained. For the first RCT, this web page differs according to ascribed Source and Messenger, Content, and Engaging factors. Participants will then be shown the video(s), followed by the questionnaires. Here, we focus not only on learning outcomes and the understanding of risk at a conceptual level but also on attitudes toward the subject, behavioral change, and compliance with the message. Gender, cultural background, age, education, and work variables will be entered as covariates in the statistical analyses and in targeted subgroup analyses.

All data collection in WP3 will be conducted online, using online surveys (Survey Monkey) and collaborative tools. With a fully digital and completely automated random-number generator and allocation procedure, video link submission and measurement instruments can be performed automatically, keeping the process free from experimenter input.

Both RCTs foresee the possibility of a longitudinal study through a follow-up survey aiming to assess whether communication outcomes (eg, learning, attitudes) persist over time, evaluate the motivation of participants to rejoin the study based on the video alternative they have been exposed to, and explore whether communication outcomes are influenced by the evolution of the COVID-19 pandemic (eg, vaccination coverage, recent infection trends).

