#### Recruitment and Sampling

Participants for the RCTs will be recruited through invites from consortium partners such as the Norwegian Air Ambulance Foundation (NAAF). Statistical power depends on a number of factors. For the first RCT, a power analysis in G*Power [43] assuming a medium effect-size (f^2^≥0.25) and a full factorial design with 5 covariates in an analysis of covariance (ANCOVA) yields a conservative sample size of 401 to achieve a statistical power of 95%. For the second RCT, a smaller sample size is needed, as there are fewer covariates. The NAAF database of financial supporters consists of approximately 150,000 people from the general public, and recruitment of only a small fraction of them (1%) will thus suffice for the intended power.

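### The no-loss hypothesis on scientific precision is worded as absence of significance, so a small real loss (about 0.2 SD or less at N = 401) could readily be read as no loss

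*Protocol article*

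**What the plan says.** The hypotheses stand in the last paragraph of the Introduction. Two are directional: shorter, props-driven videos should do better on comprehension, and narratives and metaphors should do better on intentions and behaviour. The next one is of another kind: "optimizing communication for accessibility by reducing scientific precision will not significantly reduce comprehension, intensions, or active behavior". It predicts no loss on three outcomes, and its only yardstick is significance.

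The only inferential method named is in Recruitment and Sampling under Phase 3. The first trial is sized "assuming a medium effect-size (f^2^≥0.25) and a full factorial design with 5 covariates" in an ANCOVA, which "yields a conservative sample size of 401 to achieve a statistical power of 95" per cent. On the other trial the article says: "For the second RCT, a smaller sample size is needed, as there are fewer covariates". It gives no number for it.

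The section Randomized Controlled Trials describes "2 RCTs with a factorial between-subjects experimental design including various factors related to the video communication". It does not list a precision factor by name, does not say which trial tests this hypothesis, and leaves the final choice of nonvisual factors to earlier phases.

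**The concern.** A difference test suits the directional hypotheses, because there the prediction is met by rejecting the null. For the precision hypothesis the predicted result is a failure to reject, and that can mean either no loss or too little information to see one. The incentive runs the wrong way: fewer participants or noisier questionnaires make the prediction easier to meet.

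At stake is a practical conclusion. The project intends to give communicators and health authorities evidence-based tools, and a finding that simplification costs nothing in comprehension or behaviour is one they could apply on a mass scale, where a small loss per viewer may matter.

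**Working it through.** **The plan's own figure.** The inputs given are a medium effect printed as f² ≥ 0.25, five covariates, 95% power and N = 401. Alpha, numerator degrees of freedom and number of groups are not stated, so 401 cannot be reproduced from the text alone. With the noncentral F (λ = f²N, alpha 0.05 assumed) and f = 0.25:

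- 1 numerator df needs 210–211, 3 df 279–280 and 7 df 357–358.
- About 10 df needs 400–402, which matches.
- Taken literally as f² = 0.25 (f = 0.5), the need is only about 55–150.

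The label f against f² is a separate matter. What counts here is that 401 was chosen to detect a difference, not to exclude a loss of a stated size. For two equal groups d = 2f, so f = 0.25 is a difference of 0.5 SD.

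**Chance that a real loss is non-significant.** Assumptions, none fixed by the article: a two-level precision factor, balanced, whole sample used, two-sided alpha 0.05, no variance removed by covariates.

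SE of the standardised difference = 2/√N. At N = 401 this is 2/√401 = 0.0999.

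P(non-significant | loss d) ≈ Φ(1.96 − d/SE); the opposite tail is negligible.

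- d = 0.2: Φ(1.96 − 2.00) = Φ(−0.04) = 48%
- d = 0.3: Φ(1.96 − 3.00) = Φ(−1.04) = 15%

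| True loss | N = 401 | N = 300 (assumed) | N = 210 (assumed) |
|---|---|---|---|
| 0.1 SD | 83% | 86% | 89% |
| 0.2 SD | 48% | 59% | 70% |
| 0.3 SD | 15% | 26% | 42% |
| 0.5 SD | 0.1% | 0.9% | 5% |

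The two smaller sizes only illustrate a smaller second trial; the article gives none. A 1-df ANCOVA F test agrees with these figures to within 0.3 percentage points. The 50% point at N = 401 is d = 1.96 × 0.0999 = 0.196 SD.

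**Sensitivity at N = 401.**

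- A one-sided 5% test lowers the miss rates to 74%, 36% and 9% at 0.1, 0.2 and 0.3 SD.
- If covariates explained 20% of the variance (assumed), SE = 0.0999 × √0.8 = 0.0893, and the rate at 0.2 SD falls to Φ(1.96 − 2.24) = 39%.
- If two single cells of 50 were compared (assumed), the rates rise to 83% at 0.2 SD and 68% at 0.3 SD.

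**Power of a non-inferiority test at N = 401**, true difference zero, one-sided 2.5%: Φ(Δ/SE − 1.96).

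- Δ = 0.2: Φ(0.04) = 52%
- Δ = 0.3: Φ(1.04) = 85%
- Δ = 0.36: Φ(1.64) = 95%

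These are per outcome. If all three must succeed, power at Δ = 0.3 would be 0.852³ = 62% with independent outcomes, rising towards 85% as they become perfectly correlated.

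**Total N for a two-level non-inferiority contrast**, per outcome, at 90% / 95% power: 1,052 / 1,300 for Δ = 0.2 SD and 468 / 578 for Δ = 0.3 SD.

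**The case against.** The sentence is a prediction in an Introduction, not a decision rule. Nowhere does the article say that p > 0.05 will confirm it, and the ANCOVA is mentioned only to size the first trial. The word for significance may have been meant loosely, as substantially. The article condenses a larger plan, and a margin or an equivalence test could well sit in an analysis plan that is not shown. All of this stands as far as a missing margin goes: that absence alone is no fault. What remains is the hypothesis as printed, which has the wrong form. An analysis plan that tested non-inferiority would depart from it, so the sentence needs changing either way.

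A reader might also infer that any real loss is likely to go unseen. The figures do not support that. At N = 401 a miss is more likely than not only below about 0.2 SD, and a loss as large as the planned medium effect would almost never be missed. The samples may also be larger than 401: the article speaks of 1% of about 150,000 supporters, or 1,500 people, with no split between trials. At a 0.2 SD loss the miss rate would be Φ(1.96 − 0.2/0.0730) = 22% at N = 750 and Φ(1.96 − 0.2/0.0516) = 3% at N = 1,500. That limits the size of the problem. It does not alter the logic, since a non-significant result at any N leaves the possible loss unquantified until the interval is read.

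**Conclusion.** The point holds in limited form. The no-loss hypothesis is worded so that a null result fits it without supporting it, and the only sizing given is for detecting a medium difference. At N = 401 a loss of about 0.2 SD or less could readily be read as no loss (48% at 0.2 SD, 83% at 0.1 SD). A loss of 0.3 SD would be missed about 15% of the time. Larger losses come into play only if the second trial is much smaller or single cells are compared, and the article gives neither size.

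The figures rest on a balanced two-level contrast, two-sided alpha 0.05 and no gain from covariates. The documents do not support the stronger readings that the plan lays down a rule of accepting no loss when p > 0.05, or that real losses in general are likely to be overlooked. This is one of several hypotheses, none designated primary, and it leaves randomisation, data collection and the directional hypotheses untouched. It is worth correcting but does not undermine the trials.

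**What to change.** Restate the hypothesis as non-inferiority, separately for comprehension, intentions and behaviour: reduced precision is non-inferior on an outcome if the lower limit of the two-sided 95% confidence interval of the adjusted mean difference (reduced minus full precision) lies above −Δ. Add that a non-significant difference alone is not to be read as no loss.

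Justify Δ on substantive grounds for each outcome and fix it before data collection. Do not read it off the available sample. At N = 401, Δ = 0.36 SD has 95% power, but with a true loss of 0.2 SD non-inferiority would still be declared when the estimate exceeds −0.36 + 1.96 × 0.0999 = −0.164. The chance of that is 1 − Φ((−0.164 + 0.2)/0.0999) = 36%. Such a margin is acceptable only if a loss of that order is truly unimportant.

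Name the trial and the factor that test the hypothesis, report the power the planned sample gives at the chosen margin, and say whether all three outcomes must succeed.

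The cost is a changed sentence and a reading rule for output the same ANCOVA already produces. The no-loss claim becomes harder to establish, and a tight margin may need more participants: for 0.2 SD, 1,052 to 1,300 for one outcome, which is within the 1,500 that 1% of the supporter database represents if one trial could use them all.

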## Methods

### Study Design

The study applies a sequential mixed methods design [26], combining various qualitative and quantitative research methods.

Research in science education [27,28], health communication [29], and cognitive anthropology and psychology [30,31] suggests that people interpret new information in light of their existing beliefs. Rather than relying on scientists’ opinions only, the communication of scientific knowledge should thus be based on evidence of the audience’s relevant beliefs and what they are still missing [32,33]. Aligned with this, we apply a so-called mental models approach to developing communications as our theoretical anchor for the sequential design to communicating scientific knowledge [34]: First, identify what people need to know to make more informed decisions; second, identify what they already know and how they make decisions; third, create the communication; fourth, test its effectiveness. This approach resonates with the call for an evidence-based approach to communicating science [5,35]. Correspondingly, the project is operationalized into 3 work packages (WPs) that build on each other (Figure 1). These 3 phases of the project are described in detail in the following sections.

